#### Feasibility

To examine the process and extent of CQI implementation, we will examine whether higher ratings of relative advantage, compatibility, observability and trialability, and organization readiness to change will be correlated with higher levels of CQI implementation. CQI implementation will be assessed by ratings of PDSA Activity. Ratings of innovation attributes and organizational climate will be associated with PDSA Activity. We will test this hypothesis by regressing each staff-level outcome (relative advantage, compatibility, observability and trialability, and organization readiness to change) on PDSA Activity rating at follow-up, while controlling for baseline values of these measures. The statistical significance and direction of the coefficient on the PDSA Activity will be examined to test this hypothesis. Under similar assumptions about the ICC of responses among staff within programs, we will have 80% power (alpha = 0.05) to detect whether PDSA Activity rating predicts at least 17% of the variance (e.g., R^2^ = 0.17) of each outcome. To examine whether programs that engage in a greater number of CQI activities will experience higher levels of CQI implementation, we will assess the number of CQI activities (workshop and CQI meeting attendance, worksheet completion) by each program to assess the extent of CQI activity. CQI implementation will be assessed by ratings of PDSA Activity. We will test this hypothesis by examining the correlation between the number of CQI activities completed and PDSA Activity.

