### Study aims and hypotheses

The specific aims of this study are to 1) conduct a randomized pilot study to assess the extent to which the CQI intervention leads to process and outcome improvements in the organization, and 2) investigate implementation feasibility across the organization, including the a) processes and extent of implementation among staff, b) cost of conducting CQI, and c) sustainment of the CQI process within the programs over time. We hypothesize that clients attending the intervention programs will stay in treatment longer, achieve higher levels of treatment satisfaction, have higher rates of positive treatment compliance, and achieve higher functioning compared to clients attending control programs. We expect that staff in programs participating in the CQI intervention will demonstrate improvements in job morale, job satisfaction, and attitudes towards evidence-based practices compared with staff assigned to programs in the control condition. We also hypothesize that intervention programs would experience lower staff attrition than programs assigned to the control condition. These hypotheses are developmental and exploratory, consistent with the grant mechanism that supports the work (i.e., NIH Clinical Trial Planning Grant Program, R34).

With regard to implementation feasibility (Aim 2), we hypothesize that programs that report a greater number of facilitators than barriers to CQI implementation will achieve higher levels of CQI implementation; that higher ratings on perceptions of key elements of diffusion of innovations (i.e., relative advantage, compatibility with current work practices, ease of use, and observability of benefits [31]) will lead to greater CQI implementation; that organizational readiness to change will correlate with higher levels of CQI implementation; and that programs that engage in a greater number of CQI activities will experience higher overall levels of CQI implementation. In our evaluation of sustainment we expect that programs that show higher levels of CQI activity during the intervention will sustain more components than programs with lower levels of activity and that more positive perceptions of CQI and organizational readiness to change at the end of the intervention will predict CQI sustainment.

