#### Implementation feasibility measures

To measure feasibility, we are examining the processes and extent of implementation, implementation costs, and sustainment. We collect process and extent data in three ways: (1) through semiannual semi-structured interviews with program staff who have been involved in the CQI meetings (i.e., program supervisors and clinicians); and (2) through surveys with the entire administrative and clinical staff that measure perceptions of CQI and organizational functioning, including readiness to change.

In the semi-structured interviews with key program staff, we are collecting information on the extent and nature of implementation of the PDSA cycle and on facilitators and barriers to implementation. We examine the extent of PDSA activity using both open- and close-ended interview questions based on an interview protocol developed to measure innovation use (Levels of Innovation Use (LOU) interview by Hall & Hord [51]). We are examining the nature of the CQI Actions through open-ended questions, and progress within the PDSA cycle through close-ended questions. To determine whether programs implement the Plan-Do-Study-Act phases, we are coding how many of the stages of the PDSA cycle (0-4) and how many PDSA cycles staff achieved during the intervention period. To examine facilitators and barriers to implementation, we are using items adapted from Scheier et al. [52] and Grol and Wensing’s [53] standard items for evaluating barriers and facilitators.

Through web-based staff surveys conducted every six months, we are evaluating perceptions of CQI and organizational readiness to change. To measure perceptions of CQI, we adapted Moore and Benbasat’s [54] instrument that measures Roger’s elements of diffusion. Sub-scales of this instrument include relative advantage over usual practices (5 items; α = 0.90), the complexity/ease of use (4 items; α = 0.84), compatibility (3 items; α = 0.86), observability/demonstrability (4 items; α = 0.79), and trialability of the innovation (2 items; α = 0.71). To measure organizational readiness to change we are using Texas Christian University’s Survey of Organizational Functioning (TCU SOF) instrument [49] which measures 4 domains: motivation for change, institutional resources, staff attributes, and organizational climate.

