#### Sustainment

To examine whether perceptions of CQI and organizational readiness to change at the end of the intervention will predict CQI sustainment, we will explore bivariate relationships between innovation attributes (i.e., perceptions of the CQI’s relative advantage, complexity, observability, and trialability) and organizational climate as assessed at the end of the intervention with sustainment at end of Phase 2, examining the correlation between the two. We will have 80% power (alpha = 0.05) to detect whether PDSA Activity rating predicts at least 31% of the variance (e.g., R^2^ = 0.31) of each outcome; given the power limitations this should be regarded as a descriptive rather than inferential analysis.

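### Ease of use is hypothesized to lead to CQI implementation but is left out of the implementation regressions; compatibility is left out of the sustainment correlations

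*Protocol article*

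**What the plan says.** All references are to the protocol article.

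- **Study aims and hypotheses, implementation.** Higher ratings on four named attributes are expected to lead to greater CQI implementation: "relative advantage, compatibility with current work practices, ease of use, and observability of benefits".
- **Study aims and hypotheses, sustainment.** The expectation is worded generally: "more positive perceptions of CQI and organizational readiness to change at the end of the intervention will predict CQI sustainment". No attribute is named.
- **Implementation feasibility measures.** Perceptions of CQI are measured in the six-monthly staff survey by five sub-scales: relative advantage, observability/demonstrability, and three others described as "the complexity/ease of use (4 items; α = 0.84), compatibility (3 items; α = 0.86" and "trialability of the innovation (2 items; α = 0.71".
- **Analytic methods, Feasibility.** The aim is to see whether "higher ratings of relative advantage, compatibility, observability and trialability, and organization readiness to change will be correlated with higher levels of CQI implementation". The test is specified as "regressing each staff-level outcome (relative advantage, compatibility, observability and trialability, and organization readiness to change) on PDSA Activity rating at follow-up", adjusted for baseline, and is judged by the significance and direction of the PDSA Activity coefficient.
- **Analytic methods, Sustainment.** Innovation attributes are spelled out, after an i.e., as "relative advantage, complexity, observability, and trialability". Each is to be correlated with sustainment at the end of Phase 2, and the section calls the analysis descriptive, not inferential.

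**The concern.** The article gives three attribute lists (hypothesis, implementation test, sustainment analysis) and no two of them agree. If the plan is followed as written, the ease-of-use hypothesis for implementation gets no answer although the data to answer it are collected. For sustainment, perceived compatibility is collected but left out of the analysis of perceptions. No reason is given for either omission. With five sub-scales available and the lists in disagreement, it is also open which attributes will be reported once the data are seen.

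A smaller matter is the name of one sub-scale. Ease of use and complexity are opposite poles of the same idea, and the hypotheses are directional. A reader of the sustainment results needs to know which way the score runs.

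**Working it through.** There is no figure in the plan to reproduce here, so the check sets the lists side by side.

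| Sub-scale | Hypothesized for implementation | Measured | In Feasibility regressions | In Sustainment correlations |
|---|---|---|---|---|
| Relative advantage | yes | yes | yes | yes |
| Compatibility | yes | yes | yes | **no** |
| Complexity/ease of use | yes (as ease of use) | yes | **no** | yes (as complexity) |
| Observability | yes | yes | yes | yes |
| Trialability | no | yes | yes | yes |

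**Implementation.** Four attributes are hypothesized. Three are tested (relative advantage, compatibility, observability) and one is not (ease of use): 4 − 3 = 1. One attribute outside that hypothesis, trialability, is tested. The omission is unlikely to be a slip in a single sentence, because the same list appears both in the statement of the question and in the specification of the regression.

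**Sustainment.** The hypothesis refers to perceptions of CQI in general, so the right yardstick is the five measured sub-scales. Four are listed and compatibility is not: 5 − 4 = 1. Trialability belongs here, since it is one of the measured perceptions.

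**Across the two analyses.** Each uses four of the five sub-scales and omits a different one. Relative advantage, observability and trialability appear in both and can be compared; compatibility and ease of use cannot.

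**Naming and direction.** The measures section treats complexity/ease of use as one four-item sub-scale carrying both labels. The hypothesis uses one label and the Sustainment section the other. The article does not say whether a high score means easy or complex. If high means easy, a positive correlation with sustainment supports the hypothesis. If high means complex, the same correlation counts against it.

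**The case against.** **The omissions may be only apparent.** The Feasibility section also says in general terms that ratings of innovation attributes will be associated with PDSA Activity, which could be read as covering ease of use. But that sentence names no attribute, and the regression that follows enumerates what will be modelled without it.

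**The article is condensed.** Item scoring and full variable lists are commonly left to a fuller plan. That is fair for scoring, and the direction point is therefore only a request for clarity. It does not dispose of the lists, because the article states them and they disagree with one another.

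**Sustainment loses no confirmatory test.** This stands. The sustainment hypothesis names no attribute and the analysis is declared descriptive. What remains is that one measured perception of CQI is dropped without explanation.

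Four stronger readings are tempting, and the article does not support them:

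- *That complexity enters the sustainment analysis in the opposite direction to ease of use.* One sub-scale carries both labels and no scoring is given, so a reversal is not shown. Nor does the Sustainment section state a sign for its correlations.
- *That one of four hypothesized attributes is untested for sustainment, or that trialability is unhypothesized there.* The four named attributes are tied to implementation only.
- *That the attributes tested are generally not those hypothesized.* Three of the four are tested for implementation.
- *That replacing better scales with a less reliable one causes a measurable loss.* The square roots of the reported alphas are √0.71 = 0.84 for trialability, √0.84 = 0.92 for complexity/ease of use and √0.86 = 0.93 for compatibility. These factors describe the attenuation of correlations. In the Feasibility regressions the attribute is the outcome, and random error in an outcome reduces precision but does not by itself bias the unstandardized slope being tested. The alpha for trialability also has no bearing on whether ease of use was left out.

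**Conclusion.** The concern holds in a limited form. One of the four attributes hypothesized to lead to implementation, ease of use, is measured but has no planned test, while trialability is tested without being part of that hypothesis. In the descriptive sustainment analysis, one of the five measured perceptions, compatibility, is omitted. The complexity/ease-of-use sub-scale is named inconsistently and its direction is undefined; no error of sign is shown.

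This rests on reading the enumerated lists as complete. The i.e. under Sustainment supports that reading, as does the repetition of the list under Feasibility. The severity is minor: the point affects the second aim of an exploratory pilot, touches no efficacy comparison, and can be put right without loss of data.

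**What to change.** 1. Add ease of use to the Feasibility regressions and compatibility to the Sustainment correlations. The simplest wording is to name all five measured sub-scales in both sections. If either omission is deliberate, give the reason.
2. State that trialability is additional to the implementation hypothesis under Study aims and hypotheses.
3. Use one name for the complexity/ease-of-use sub-scale throughout and state what a high score means.

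The cost is a change of wording in the two analysis sections plus a label. The attribute regressions go from four to five, as do the attribute correlations, so there is one more result to interpret in each analysis. All five sub-scales are already in the staff survey, so no new data collection is needed.

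### The baseline-adjusted Aim 2 regression measures whether perceptions changed along with PDSA Activity, so it cannot test whether earlier perceptions lead to, or readiness correlates with, implementation

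*Protocol article*

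**What the plan says.** In the protocol article, Study aims and hypotheses gives the Aim 2 hypothesis in two strengths. Higher ratings on the diffusion elements "will lead to greater CQI implementation", whereas for readiness the claim is only that "organizational readiness to change will correlate with higher levels of CQI implementation".

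Under Analytic methods, Feasibility, both are restated as an association: the ratings "will be correlated with higher levels of CQI implementation". Implementation is then given a measure: "CQI implementation will be assessed by ratings of PDSA Activity". The test consists of "regressing each staff-level outcome (relative advantage, compatibility, observability and trialability, and organization readiness to change) on PDSA Activity rating at follow-up". A further clause sets the covariates, "while controlling for baseline values of these measures", and the result is judged as follows: "The statistical significance and direction of the coefficient on the PDSA Activity will be examined to test this hypothesis". The power sentence runs the same way, with PDSA Activity explaining at least 17% of the variance of each perception or readiness score at 80% power and alpha 0.05.

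Three facts from elsewhere bear on this. The baseline staff survey precedes study assignment (Process and outcome measures). PDSA stages and cycles are coded by program (Implementation feasibility measures). No other model in the article has implementation as the outcome and perceptions or readiness as predictors; the Sustainment section relates perceptions to sustainment.

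**The concern.** The survey that clearly precedes implementation is the baseline one. Entering it as a covariate holds constant the perceptions that could have led to implementation, and the follow-up survey comes after much of the implementation has happened. The remaining association is between change in perceptions and PDSA Activity. That is a reasonable question, but it is neither the directional hypothesis about perceptions nor the plain correlation restated under Feasibility.

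The article calls this coefficient the test of its hypothesis. A positive result could therefore be read as support for perceptions leading to implementation when it may equally reflect implementation improving perceptions. A null result could be read as evidence against the hypothesis when the hypothesis is true.

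**Working it through.** **1. The plan's own figure.** For one predictor, R2 = 0.17 gives f2 = 0.17/0.83 = 0.205. Noncentral F power (1 and n − 2 df, noncentrality n × f2) reaches 80% at n = 41, two-sided. Fisher's z gives ((1.960 + 0.842)/atanh(0.412))² + 3 = 43.8, so 44. The article gives no staff numbers, so 0.17 cannot be strictly reproduced, but it agrees with the 0.63 SD figure under Intervention efficacy: 2 × ((1.960 + 0.842)/0.63)² = 39.6, so 40 effective staff per arm. At ICC 0.040 that is about 16 staff in each of 4 programs: 64/(1 + 15 × 0.04) = 64/1.60 = 40. The power figure is not at fault.

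**2. Orientation.** In a single-level linear model with the same covariate, the t statistic depends only on the partial correlation, which is symmetric. Swapping outcome and predictor left the p-value unchanged in every simulated run (largest difference about 5 × 10⁻¹⁴).

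**3. What the coefficient measures.** Let P0 and P1 be baseline and follow-up perceptions and A be PDSA Activity, all standardised. The planned coefficient is Cov(P1, A | P0)/Var(A | P0).

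- *Case A, baseline perceptions drive implementation.* A = R·P0 + e and P1 = ρ·P0 + u, with e and u independent. Then Cov(P1, A | P0) = Cov(u, e) = 0. Yet Corr(P0, A) = R = √0.17 = 0.412 and Corr(P1, A) = ρR = 0.7 × 0.412 = 0.289. The hypothesis and the plain correlation both hold, and the tested coefficient is zero.
- *Case B, implementation drives later perceptions.* P1 = ρ·P0 + R·A + u, with A independent of P0. The coefficient is R = 0.412, while Corr(P0, A) = 0.

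Simulation, 5,000 runs each (ρ = 0.7 and R2 = 0.17 assumed; observations treated as independent):

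| Case | n | Planned test rejects | A regressed on P0 rejects |
|---|---|---|---|
| A | 42 | 5.0% | 79% |
| A | 200 | 4.9% | 100% |
| B | 42 | 98% | 4.9% |
| B | 200 | 100% | 4.9% |

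The 98% and 79% are not like with like: in case B, A explains 0.17/(1 − 0.49) = 0.33 of the variance left after adjustment. The result that matters is that case A stays at alpha whatever n is. A program-level version of case A (8 programs, ICC 0.04, assumed r = 0.8, 6 or 16 staff per program) rejects in 6% or 7% of runs.

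**4. Perceptions formed after baseline.** If perceptions formed during exposure drive implementation (8 programs, 16 staff each, r = 0.8 and ρ = 0.7, all but the 8 assumed), the planned test rejects in 22% of runs at ICC 0.04 and 50% at ICC 0.20. A rank correlation of PDSA Activity with baseline scores then rejects in only 5–7%.

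**5. Precision of the forward analysis.** With program as the unit, the R2 detectable at 80% power is about 0.59 for 8 programs (r = √0.59 = 0.77) and 0.89 for 4 (r = 0.94). As an illustration, an observed correlation of 0.5 over 8 programs has a 95% interval on Fisher's z of 0.549 ± 1.96/√5 = −0.327 to 1.426, or −0.32 to 0.89 as a correlation.

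**6. Variables.**

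| Scale | Hypothesised | Measured | In the Feasibility analysis |
|---|---|---|---|
| Relative advantage | yes | yes | yes |
| Compatibility | yes | yes | yes |
| Ease of use | yes | yes (4 items) | no |
| Observability | yes | yes | yes |
| Trialability | no | yes | yes |
| Readiness | yes | yes | yes |

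**The case against.** The strongest defence has four parts.

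*The orientation is ordinary.* Staff answer the surveys and PDSA progress is scored by program, so a staff-level outcome with a program-level predictor respects the nesting. This stands. A reader might infer that having perceptions on the left is itself the error; step 2 shows that it is not.

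*Much of the hypothesis is associational.* For readiness the article claims only a correlation, and Feasibility restates the rest that way. This stands as far as it goes, and no causal claim about readiness should be attributed to the article. It does not rescue the model, because in case A the plain correlation is 0.289 or 0.412 and the baseline-adjusted coefficient is zero. Nor does the article say how a significant coefficient will be worded; the risk lies in calling it a test of the hypothesis.

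*The test is not blind under every reading.* Staff meet the PDSA cycle only after baseline and randomization, so the perceptions that matter may form later. This stands. A reader might infer that the planned test has almost no chance of detecting a true hypothesis; that holds only if baseline perceptions are the driver. Step 4 shows some power otherwise, and there the baseline correlation does poorly. Even then the planned coefficient cannot say which way the association runs.

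*Low power here is mostly the small design.* This stands for the forward analysis: with 8 programs, ICC 0.04 and a true r of 0.8, it rejected in only 13–27% of simulated runs. It does not explain case A, where the planned test stays at 4.9% with 200 observations.

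The missing ease-of-use scale may be a loosely copied list. It is a minor point, but the current text leaves a hypothesised and measured scale untested.

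**Conclusion.** The concern holds in this form: baseline adjustment together with follow-up timing makes the PDSA coefficient a measure of concurrent change, without direction. It cannot be read as support for perceptions leading to implementation, and it does not test the plain correlation that Feasibility restates.

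The algebra of case A needs only that pre-intervention perceptions drive implementation and nothing runs back. The rejection rates also rest on assumed values: baseline to follow-up correlation 0.7, R2 0.17 or r = 0.8, and the staff numbers. They illustrate the mechanism and do not predict this trial's results.

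Severity is moderate. This is one Aim 2 analysis in an exploratory pilot; randomization, the Aim 1 efficacy comparisons, costs and sustainment are untouched. A reader might infer a flaw in the trial as a whole, which the article does not support.

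**What to change.** 1. For the stated hypothesis, relate program-level PDSA Activity (stages reached, cycles completed) to program-mean baseline scores on each hypothesised perception scale, including ease of use, and on readiness. Do not adjust those scores away. Report correlations with intervals over at most 8 programs and label them descriptive, as the Sustainment section already does for its own analysis. State that the R2 = 0.17 power figure does not carry over.
2. Keep the present regression under its own label, asking whether change in perceptions and readiness is associated with PDSA Activity, and draw no directional conclusion from it.

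A survey taken just before the first CQI Action would be a better predictor, but is probably not available: surveys are six-monthly and the planning stage covers the first three monthly meetings. The report should say that baseline scores may miss perceptions formed during exposure.

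The cost is analysis wording only, since the data are already part of the planned collection. The price is an imprecise analysis that is openly descriptive.

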### Analytic methods

The randomization of programs to study conditions is necessary given the CQI intervention is intended to change program-level practices. However, it is important to assess the effect of the multilevel study design on the statistical power to detect intervention effects [57]. One key component of the power calculations is the intra-cluster correlation (ICC), which is the proportion of the overall variance in the outcomes that is attributable to program membership. For a given sample size, statistical power decreases as ICC increases. We therefore present below our analytic approach for the analysis of each outcome, and note for which outcomes we expect to have sufficient statistical power to examine, based on ICC data from previous studies.

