#### Intervention efficacy

The first set of analyses will focus on examining the effect of the CQI intervention on staff outcomes relative to the control condition (Aim 1). The hypotheses related to staff outcomes are that staff participating in the CQI intervention will demonstrate improvements in: a) job morale, b) job satisfaction, and c) attitudes towards EBPs as compared with staff assigned to the control condition. Improvement will be measured as the difference between pre-intervention and post-intervention (i.e., end of Phase 1) assessments. Improvement in staff-level outcomes will be modeled using linear multilevel regression modeling, controlling for baseline values of job morale (a), job satisfaction (b), and attitudes towards EBPs (c) when modeling those outcomes. The multilevel model structure will account for the similarity, or intra-cluster correlation (ICC), among staff outcomes within the program. The statistical significance of a dichotomous predictor of participating in the CQI intervention and its direction will be examined to test these hypotheses. We will also examine whether programs that participate in the CQI intervention experience lower staff attrition than programs assigned to the control condition (d). Given the sample size of programs in the study, we will use descriptive statistics to examine whether staff attrition is lower for staff participating in the CQI intervention.

For analyses of the staff-level outcomes (a-c)*,* we assume an intra-cluster correlation (ICC) of 0.040 for staff-level outcomes, which is obtained by averaging ICCs for data on similar measures from two external studies. One ICC estimate is from staff attitudes toward implementing ‘Getting To Outcomes,’ a site-level intervention that incorporates CQI and other elements to increase organizational evaluation capacity [58]. Other ICC estimates are for subscales from the Organizational Readiness for Change (ORC) instrument [49] that was implemented at four SUD treatment program sites from same organization participating in a prior RAND study [59]. We will have 80% power (alpha = 0.05, two-sided test) to detect an effect size of 0.63 standard deviations (SDs). Our analyses of staff attrition (d) will be limited to exploratory analyses given the lack of statistical power for formally testing whether CQI has an effect on attrition.

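### The 80% power for PDSA Activity to explain 17% of staff-level variance does not fit the article's ICC of 0.040, and it counts about 40 effective staff as independent although the rating varies only between programs

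*Protocol article*

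**What the plan says.** - **Predictor.** Under Implementation feasibility measures, PDSA Activity is coded from interviews with the staff who attend CQI meetings, as stages reached (0 to 4) and number of cycles. The stated purpose is "To determine whether programs implement the Plan-Do-Study-Act phases". The Feasibility section later correlates it with counts of CQI activities taken for each program. The article does not call the rating a program-level variable, but both places point that way.
- **Outcomes.** These are whole-staff survey scores: relative advantage, compatibility, observability and trialability, and organizational readiness. Each is regressed on the PDSA rating with baseline adjustment, and the coefficient's significance and direction serve as the test.
- **Power.** "Under similar assumptions about the ICC of responses among staff within programs", the section states that "we will have 80% power (alpha = 0.05) to detect whether PDSA Activity rating predicts at least 17% of the variance" of each outcome, an R² of 0.17.
- **ICC.** Analytic methods defines it as a quantity "which is the proportion of the overall variance in the outcomes that is attributable to program membership". Intervention efficacy gives the value: "we assume an intra-cluster correlation (ICC) of 0.040 for staff-level outcomes", averaged from external studies.
- **Not stated.** The article does not give the number of staff, whether four or eight programs enter this regression, or whether the ICC is before or after conditioning on the predictor.

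**The concern.** All staff in a program share the same PDSA value. Such a predictor can account for differences between programs but not for differences among colleagues in one program. On the article's definition only 4% of the variance lies between programs, yet the power statement is built on 17%.

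The second difficulty is the unit of information. A rating with one value per program takes at most four or eight distinct values. Deflating the staff count by a design effect adjusts the variance of the estimate, but it does not give the test the degrees of freedom of 40 independent people.

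What is at stake is how the result is read. The test is judged by significance, with 80% power and no caveat. The Sustainment section marks its parallel analysis as descriptive because power is limited, and Intervention efficacy confines staff attrition to exploratory analysis. Beside these, a reader would take the Feasibility test as adequately powered.

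**Working it through.** **1. Reproducing the 17%.** For one predictor, noncentral F, alpha 0.05, noncentrality n·R²/(1−R²):
- n = 40 gives a detectable R² of 0.171; power at R² = 0.17 is 79.7%.
- n = 20 gives 0.305, matching the 31% in the Sustainment section.

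The effective n is J·m / [1 + (m−1)·0.04], for J programs with m staff each. No staff number is stated, so m is backed out, taking four programs per cohort:
- 8 × 6: 48/1.2 = 40. Four programs give 24/1.2 = 20, which fits the 31%. The 0.63 SD for staff outcomes follows if a baseline correlation of 0.7 is applied: 2.80 × √(2/20) × √(1−0.49) = 0.63.
- 4 × 16: 64/1.6 = 40. The 0.63 SD follows without adjustment: 2.80 × √(2/40) = 0.63. The 31% is not reproduced this way.

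Both give the 17%, and the article does not settle which was used.

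**2. The ceiling under the stated definition.** Scale total variance to 1 and let the outcome be the PDSA effect plus a program residual plus a staff residual. Between-program variance = R² + residual program variance = ICC, so R² ≤ 0.04, and 0.17/0.04 = 4.25. Baseline adjustment with within-program correlation r raises the ceiling for the partial R² to 0.04/[0.04 + 0.96(1−r²)]. At r = 0.7 (stated in the footnote to Table 1, for client outcomes only) this is 0.076; 0.17 is reached only at r of about 0.89. At R² = 0.04, the effective-n method gives 24% power (n = 40). An unadjusted program-level test gives 22% (8 × 6) or 17% (4 × 16).

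**3. The residual reading.** If 0.040 is the ICC left after the predictor, residual program variance is 0.83 × 0.04 = 0.0332 and the total between-program share is 0.17 + 0.0332 = 0.203.

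**4. Power at R² = 0.17 on that reading, at program level.** Staff variance is 0.83 − 0.0332 = 0.7968. The error variance of a program mean is 0.0332 + 0.7968/m. The noncentrality is √[J·0.17/error variance], on J−2 df, treating the ratings as fixed.

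| Programs × staff | Error variance | Noncentrality | Critical t (df) | Power |
|---|---|---|---|---|
| 8 × 6 | 0.166 | 2.86 | 2.447 (6) | 67% |
| 4 × 16 | 0.083 | 2.86 | 4.303 (2) | 36% |

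The effective-n calculation has the same noncentrality, √(40 × 0.17/0.83) = 2.86. The fall from 80% therefore comes entirely from using 6 or 2 df in place of 38.

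**5. With baseline adjustment, assuming r = 0.7 within programs.** Staff variance becomes 0.7968 × 0.51 = 0.406.
- 8 × 6: error variance 0.101, noncentrality 3.67, power 86%.
- 4 × 16: error variance 0.0586, noncentrality 3.41, power 46%.

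**6. More staff.** Eight programs with 10 staff each give 82% unadjusted at program level. But the effective n is then 80/1.36 = 58.8 and the effective-n method would have given a detectable R² of 0.121, not 0.17.

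**The case against.** A reader might infer that the claim is impossible and that no attainable association could reach 80% power. The documents do not support that.

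- The 80% is a conditional statement and reproduces, so it is not an arithmetic slip.
- Design-effect calculations ordinarily use a residual ICC, and the article's other figures fit that reading. An effect of 0.63 SD in two equal arms is R² = (0.63²/4)/(1 + 0.63²/4) = 0.090, already above 0.040. In Table 1, 6.6 points on positive compliance is an R² of about 0.0047 against an ICC of 0.002.
- The ICC is only said to be similar to 0.040, and comes from external data.
- With eight programs, program-level power can pass 80% if baseline adjustment is strong or staff are more numerous.

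Nor can one say that the 17% arises in only one way, since 8 × 6 and 4 × 16 both give it. Nothing in the article says a null result would be taken as evidence of no association. This is also a secondary analysis in an exploratory pilot, and no efficacy conclusion depends on it.

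These points rule out the stronger reading. They do not remove the conflict with the article's own definition of the ICC, the unstated share of about 0.20 that the residual reading needs, or the use of staff-level degrees of freedom for a program-level predictor. A condensed article may leave staff numbers to the full plan, but here it states a power figure and a definition that do not agree.

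**Conclusion.** The concern holds as an inconsistency. Under the ICC as the article defines it, a detectable R² of 0.17 is more than four times the largest value a program-level rating could reach. Under a residual ICC it is possible, but only with about a fifth of the variance lying between programs.

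Even then, neither staffing pattern shown here to reproduce the 17% gives 80% unadjusted power at program level: about 67% for 8 × 6 and 36% for 4 × 16. The first reaches about 86% only with a baseline correlation borrowed from client outcomes; the second reaches about 46% with the same assumption.

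This rests on PDSA Activity being one value per program (inferred, but well supported), back-calculated staff numbers, equal program sizes, and ratings treated as fixed. If the ratings are treated as random normal values, unadjusted power for 8 × 6 falls further, to about 56%.

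**What to change.** In the Feasibility section, replace the 17%/80% statement with power, or a detectable R², computed at program level on the number of programs minus 2 degrees of freedom. State how many programs and staff enter, whether the ICC is total or residual, and any baseline correlation assumed. If these cannot be given, withdraw the statement. In either case, label the analysis descriptive, as the Sustainment section does for its own.

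The cost is a sentence or two and the loss of a power claim. Data collection, sample and regression model are unchanged.
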